### Safety End Points

To assess the safety of the intervention, the following adverse events were defined and recorded at 8 weeks and at 6 months, respectively: (1) new occurrence or worsening of suicidal ideations during the intervention and follow-up period (recorded via item 9 of the PHQ-9), (2) illnesses and injuries during the intervention and follow-up period (self-report), and (3) inpatient treatment during the intervention and follow-up period (self-report).

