## Methods

### Study Design

We are conducting a monocenter 2-arm randomized controlled trial with 3 assessment points (baseline, postintervention at 8 weeks, and follow-up at 6 months). Participants in the intervention condition will receive access to MindDoc with Prescription in addition to care as usual. Participants in the control condition will only have access to care as usual. Care as usual includes any form of treatment, including psychotherapy, unless psychotherapy has already been started or planned at the time of inclusion in the study. The study design is illustrated in Figure 1.

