#### Exclusion Criteria

We are excluding individuals who receive outpatient psychotherapy or inpatient treatment for a mental disorder at the point of enrollment or already have such a treatment planned to start within the next 8 weeks. We are also excluding individuals who report changes in antidepressant medication in the past 4 weeks, who report suicidal ideations, or who have a history of bipolar disorder, psychotic disorder, substance use disorder, or suspected substance use disorder. Individuals who report having used the MindDoc App or a comparable digital intervention in the past 12 months will also be excluded.

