#### Study End Points

##### Depression Symptom Severity

Depression symptom severity is assessed using the depression module of the PHQ-9 [53,58], a 9-item questionnaire that is part of the Primary Care Evaluation of Mental Disorders (PRIME-MD) diagnostic instrument for common mental disorders [54] and can be self-administered. The questionnaire evaluates each of the 9 DSM-5 diagnostic criteria for depression [59], with scores ranging from 0 (not at all) to 3 (nearly every day). The PHQ-9 is a reliable and valid tool for measuring depression, with a Cronbach α coefficient of .89.

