Since suicidal ideations are among the symptoms of depression, they may occur during the intervention or follow-up period even in participants who did not report them at baseline. In this case, precautions will be taken: (1) participants will receive written information about help resources immediately after completing assessments and (2) the study team will be informed and a member will promptly contact participants to further assess the situation. If a crisis cannot be resolved or a participant cannot be reached, support from local emergency services will be sought and the participant’s contact information will be shared with these services. Participants agree to this procedure upon enrollment in the study.

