## Discussion

### Anticipated Findings

Data from this study will be used to establish whether access to an app-based, self-guided, transdiagnostic intervention addressing common mental disorders is associated with an improvement of depression symptoms in individuals diagnosed with mild or moderate depression and with or without comorbid mental disorders. It will also be used to investigate improvements in quality of life, anxiety symptoms, and patient empowerment and self-management behaviors in relation to access to the intervention.

The results will provide additional insights into the therapeutic alliance in digital interventions and also assess their safety by systematically collecting data on negative intervention effects.

The study will contribute to the evidence base on transdiagnostic digital interventions and at the same time provide information on what role primary care providers can play in facilitating the dissemination of digital mental interventions.

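### Suicidal ideation is defined as a safety event over the whole follow-up, but its only named source is PHQ-9 item 9 at 8 weeks and 6 months, so the period incidence is understated in both arms

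*Protocol article*

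**What the plan says.** Under Safety End Points the article lists three adverse events. It introduces them with the statement that "the following adverse events were defined and recorded at 8 weeks and at 6 months, respectively". The first is "new occurrence or worsening of suicidal ideations during the intervention and follow-up period (recorded via item 9 of the PHQ-9"). The other two, illnesses or injuries and inpatient treatment, are worded for the same period and taken from self-report.

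Under Depression Symptom Severity, PHQ-9 items are described as frequency ratings, "with scores ranging from 0 (not at all) to 3 (nearly every day"). Neither that section nor any other states how far back item 9 asks, or says that it was reworded to cover the time since the last assessment.

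Under Study Design there are "3 assessment points (baseline, postintervention at 8 weeks, and follow-up at 6 months"). Under Exclusion Criteria, applicants "who report suicidal ideations" are not enrolled. Under Ethical Considerations the authors accept that suicidal ideations are a symptom of depression and that "they may occur during the intervention or follow-up period even in participants who did not report them at baseline". The first precaution named there is tied to the surveys: "participants will receive written information about help resources immediately after completing assessments".

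**The concern.** The event as worded and the event as measured are different quantities. The wording describes a cumulative incidence: did ideation appear or get worse at any time over about 26 weeks? The named source gives two readings of a frequency item, one at week 8 and one at about week 26. If the item looks back only a short way, ideation that began and ended well before an assessment scores 0 there and enters the data as no event.

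This matters because the authors themselves expect ideation to emerge during the trial, and because the trial is meant to support reimbursement of the app, where a statement about safety carries weight. A low count on this end point could be read as showing that little ideation occurred over six months. The data could support only the narrower statement that little was reported at two assessments.

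**Working it through.** The plan gives no figure for this end point, so there is nothing of its own to reproduce. The check asks how much of the period two assessments can reach.

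**Inputs**
- Assessments at week 8 and at 6 months, taken as week 26 (Study Design; Safety End Points). The gaps are 8 and 26 − 8 = 18 weeks.
- Look-back of item 9, *w*: not stated. Assumed range 2 to 4 weeks, with 0 weeks and the full interval as limits.
- Episode length, *L*: not stated. Illustrated with 1 and 4 weeks.
- Onset of an episode: assumed uniform over the 26 weeks.

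**Step 1: share of calendar time covered**

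Coverage = [min(*w*, 8) + min(*w*, 18)] / 26.
- *w* = 0: 0%.
- *w* = 2: (2 + 2)/26 = 15.4%. By interval, 2/8 = 25% of the first and 2/18 = 11% of the second.
- *w* = 4: (4 + 4)/26 = 30.8%. By interval, 4/8 = 50% and 4/18 = 22%.
- *w* = 18, the whole longer gap: (8 + 18)/26 = 100%.

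**Step 2: chance that an episode is seen**

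Coverage of time is not detection of episodes, because an episode has duration and needs only to overlap a window. An episode of length *L* overlaps the window before an assessment at time *t* if it starts between *t* − *w* − *L* and *t*. With two assessments, and as long as *w* + *L* is at most 8 weeks, the chance is 2(*w* + *L*)/26.

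| Look-back *w* | 1-week episode | 4-week episode |
|---|---|---|
| 0 weeks | 2/26 = 7.7% | 8/26 = 30.8% |
| 2 weeks | 6/26 = 23.1% | 12/26 = 46.2% |
| 4 weeks | 10/26 = 38.5% | 16/26 = 61.5% |

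These figures assume that both assessments are completed and that a person reports any ideation inside the window. The Results section gives about 20% missing values in the primary outcome. That outcome is the PHQ-9 total at 8 weeks, so item 9 is probably missing at 8 weeks for a similar share, which lowers the figures further.

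**Step 3: what worsening can capture**

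Because applicants reporting ideation are excluded, item 9 should be 0 at baseline for nearly everyone. At 8 weeks a rise from baseline is then almost the same as new occurrence. At 6 months the comparison with 8 weeks is informative: a participant with new ideation at 8 weeks can score higher at 6 months. The term therefore has content, but the article does not say which earlier value it refers to.

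**The case against.** Several stronger readings are tempting, and the article does not support them.

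- *A reader might infer that any episode resolving between assessments is lost.* That goes too far. Item 9 is a frequency item and looks back, so an episode that ends inside the window can be counted. One that led to admission would also appear under inpatient treatment, though not as ideation.
- *A reader might take 15% to 31% as the detection rate.* Those are shares of calendar time. Detection is higher, as Step 2 shows, and all these figures rest on a look-back that the article does not state.
- *A reader might infer that worsening is empty because ideation is excluded at entry.* Deterioration from 8 weeks to 6 months remains possible, and dropping the term would lose it.
- *A reader might set the end point against the promise, under Anticipated Findings, to "assess their safety by systematically collecting data on negative intervention effects".* Under Other Measures that term belongs to the INEP-ON questionnaire, so the sentence is not a claim about item 9. Nor does the article describe INEP-ON as a measure of ideation.
- *A reader might infer that nothing detects ideation between assessments.* The article condenses a fuller protocol, and event-driven reporting may stand there. Its absence here is no finding.
- *A reader might infer that the comparison between arms is biased.* Nothing shows that detection would differ by arm.

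The best remaining objection is that this is only a matter of wording, in an end point that does not touch the primary analysis. It is true that the primary analysis is untouched. But the mismatch lies in the stated definition and its stated source, not in something left unsaid, and it determines what the safety result may be said to show.

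**Conclusion.** The concern holds in this form: an event defined over about 26 weeks is to be taken from item 9 at two assessments, so episodes outside the item's look-back are not counted and the period incidence is understated in both arms. With an assumed look-back of 2 to 4 weeks and uniform onset, about 23% to 38% of 1-week episodes and about 46% to 62% of 4-week episodes would be seen. The understatement would disappear only if item 9 asked about the whole time since the last assessment, which the article does not say. The point should be corrected because it limits the safety conclusion. It does not affect the efficacy result, and it is no evidence of a difference in harm between the arms.

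**What to change.** 1. Define and report the end point as ideation reported on item 9 at 8 weeks and at 6 months: prevalence at each assessment, by arm, with the number who answered. Do not describe it as occurrence during the period. State the item's look-back. This costs nothing and applies equally to participants already assessed.

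2. Keep worsening, and define it as a higher item 9 score than at the previous assessment: baseline for the 8-week value, 8 weeks for the 6-month value. State which value serves as reference if the 8-week one is missing.

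3. Optionally, add one self-report question on ideation since the last assessment to the remaining surveys in both arms. Report it separately from item 9, so that the event definition does not differ between early and late participants. The cost is one survey item and an amendment notified to the ethics committee and the registry. The drawbacks are recall over up to about 18 weeks and missing data for those already assessed: by September 5, 2023, 176 of the 275 included had already given the 8-week outcome.

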### Sample Size

The primary end point is the between-group difference in depressive symptoms (PHQ-9 total score) after 8 weeks. The effect regarding the primary end point will be determined by a 2-tailed *t* test. Based on the results of our previous study, an effect of *d*=0.4 (Cohen *d*) is expected and a dropout rate of up to 60% is assumed. A sample size of 570 participants is required to detect the expected difference at 85% probability and α=5% significance in both intention-to-treat and per-protocol analyses.

### Data Management

#### Study Data

All study data are collected and stored in an electronic data capture system (Climedo) in the form of electronic case report forms and electronic patient reported outcome forms All data collected by means of the EDC provided by Climedo Health GmbH are processed and stored in data centers in Frankfurt am Main, operated by Amazon Web Services EMEA SARL (Luxembourg), which acts as an order processor for Climedo Health GmbH. Amazon Web Services is currently ISO 27001, ISO 27017, and ISO 27018 certified hosting provider. The ISO 27001 certification largely corresponds to the requirements of the German Federal Office for Information Security and is compatible with these (eg, BSI-200). ISO 27017 is an international standard for securing cloud services (Cloud Security), while ISO 27018 primarily relates to the protection of personal data (Cloud Privacy). All personal data are stored on servers in Germany. After completion of the data collection, the pseudonymized data will be exported by MindDoc Health GmbH and stored there in digital form for a period of 10 years in accordance with legal requirements.

All data collected from participants will be assigned an 8-digit code consisting of random numbers and letters. Personal information, including name and contact details, are only collected from those participants who do not meet any exclusion criteria in the screening.

A pseudonymization list of names assigned to codes is stored in a protected area of the electronic data capture system, only accessible to authorized members of the study team. The data are protected from unauthorized access, allowing for secure study procedures. The list will be destroyed after the study completion or after 10 years.

All data collected will be handled in accordance with national law and the GDPR. All personal and health data will be stored and handled in accordance with international and national data protection guidelines. Any publication derived from the personal data will be presented in such a way that it is impossible to identify individuals by referring only to group-level statistics. Participants have the right to request the deletion of their records prior to the destruction of the pseudonymization list without giving any reason.

#### App Data

To use the digital health app, participants must create a user account with a name and email address of their choice, stored separately by MindDoc Health GmbH. Passwords must meet minimum security standards that are checked in real time by an algorithm. Forgotten passwords cannot be recovered and a new password can be set through a link sent via email.

Using the app generates additional usage data (eg, answers, mood ratings, and course or exercise usage) stored by MindDoc Health GmbH. These data can be merged with study data in pseudonymized form using personalized access codes and a 16-digit user ID.

All data collected as part of the app are processed and stored in a high-security data center in Germany. The data center is operated by T-Systems International GmbH, [name], which acts as an order data processor for MindDoc Health GmbH. All personal data are stored on servers in Germany. Separate consent is obtained for the processing of health data pursuant to Article 9 (2) lit h DS-GVO within the app, without which the app cannot be used. Irrespective of the right to data deletion pursuant to Art. 17 DS-GVO, the data collected in the app can be deleted from the server directly in the app in the “Settings → Data & Security” area at any time. Prior to this, they can be transferred to the user’s own device using an export function.

All communication between the user and the technical platform is automatically encrypted. The app communicates with the server over encrypted connections using transport layer security or hypertext transfer protocol secure, which prevents third parties from unauthorized reading of the data while it is being sent (ie, “in transit”). Both servers and databases are located behind firewalls to prevent access to data while it is being stored (ie, “at-rest”) or while it is being processed (ie, “in process”). In order to independently check system security, test attacks (penetration tests) are carried out at least once a year by an externally contracted IT security company on the servers provided and attempts are made to gain unauthorized access to them on a test basis.

### Statistical Analysis

Data will be described using descriptive statistics (eg, frequencies, mean, median, SD, and IQR) and visualizations (eg, histograms, box plots, and bar charts). Assumptions for statistical tests will be checked (eg, normality by histograms and tests, sphericity by Mauchly test, and equal variance-covariance matrices by Box and Levene tests). App usage will be described according to previously proposed standards for reporting adherence to digital interventions [69], and include days of use and engagement with different features of the app.

Significant baseline group differences will be detected using *χ*^2^ and *t* tests on baseline variables and accounted for in all analyses.

The intervention’s effectiveness will be analyzed using an intention-to-treat approach with multiple imputed data. Missing values from the postsurvey and follow-up survey of nonbinary end points will be imputed using all available information collected at baseline by applying an iterative Markov chain Monte Carlo method based on the initial group assignment. For this purpose, imputations will be calculated for 100, 150, 200, 300, 400, and 500 iterations. Then, the fraction of missing information (FMI) index will be determined for all multiply imputed data sets. The FMI ranges from 0 to 1 (where 1 means that 100% of the information required for the planned conclusions is missing) and is a reliable indicator of the validity of conclusions based on imputed data sets [70]. For the following analyses, the number of imputations that do not result in further improvement in FMI compared to previous imputations will be chosen. Statistical characteristics will be aggregated across the multiply imputed data sets using Rubin’s rules. The comparison of intervention effects on all outcomes will be done using *t* tests.

In addition to the primary analysis, further sensitivity analyses will be performed. Analyses of intervention effects on all outcomes will be repeated using analysis of covariance, adjusted for baseline scores. In addition, per-protocol analyses excluding participants who violated the protocol will be conducted. The following protocol violations have been prespecified: (1) failure to download the app and complete the onboarding process in the intervention group, (2) reporting of using a similar digital health intervention during the intervention and follow-up period in the control group, (3) reporting of regular psychotherapy during the 8-week intervention period, and (4) noncompletion of postintervention or follow-up assessment. Subgroup analyses will be done to address potential heterogeneity.

To allow for adjustment of the sample size in this study (for lower dropout), an interim analysis can be performed. This can be done once the primary end point of 182 participants is available. With this sample size, the expected effect can be revealed with a probability of 85% at a significance level of α=10%. The interim analysis will be performed blinded, meaning that the variable “group membership” will be replaced by a dummy variable and the blinded data set will be analyzed by a person who is not part of the core study team and is unaware of the group assignment.

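### Covariates for all analyses are to be picked by significance tests of baseline differences, which makes the primary model depend on chance and conflicts with the t test named for the primary end point

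*Protocol article*

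**What the plan says.** Four statements in the protocol article bear on the primary model.

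- **Statistical Analysis, covariate rule.** "Significant baseline group differences will be detected using" χ² and t tests, and they are to be dealt with by "tests on baseline variables and accounted for in all analyses". The section gives no list of variables, no significance level and no form of adjustment.
- **Statistical Analysis, test.** After multiple imputation and pooling by Rubin's rules: "The comparison of intervention effects on all outcomes will be done using" t tests.
- **Sample Size.** "The effect regarding the primary end point will be determined by a 2-tailed" t test.
- **Statistical Analysis, sensitivity analyses.** "In addition to the primary analysis, further sensitivity analyses will be performed". Among these, the analyses of all outcomes are "repeated using analysis of covariance, adjusted for baseline scores".

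Procedures gives 1:1 randomisation stratified by sex, diagnosis and previous psychiatric or psychotherapeutic treatment. These factors are not named as covariates in any analysis.

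**The concern.** There are two linked problems.

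First, the selection rule is unsound. With proper randomisation, a significant baseline difference is a chance event. Its p-value reflects the luck of the allocation and carries no information on whether the variable predicts the 8-week PHQ-9 score. The rule can therefore bring in a variable of no prognostic value. It keeps baseline PHQ-9, likely a strong predictor, out of the primary model whenever its difference falls short of significance.

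Second, the rule conflicts with the named test. A two-sample t test has no covariates. Once one baseline difference is significant, the analyst cannot both adjust in every analysis and compare the groups by t test. The ANCOVA does not settle this, because it is labelled a sensitivity analysis and adjusts for baseline scores, which need not be the variables flagged.

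At stake is which estimate and p-value count as the primary result. The Dissemination section says the trial is meant to support registration for reimbursement, so this should be known before the data are seen.

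**Working it through.** **Inputs from the document.** d = 0.4, power 85%, two-sided α = 5%, N = 570 and "a dropout rate of up to 60% is assumed" (Sample Size); 1:1 allocation (Procedures).

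**Assumptions, because the document gives no figures.** Number of baseline tests k, their 5% level, their independence, and the correlation r between baseline and outcome.

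**Step 1: the plan's own figure.** The normal approximation is n per arm = 2(z₀.₉₇₅ + z₀.₈₅)²/d² = 2(1.960 + 1.036)²/0.16 = 112.2, so 113. The noncentral t calculation gives 114 per arm, 228 in total. Then 228/(1 − 0.60) = 570, an exact match. The sample size is built on an unadjusted t test.

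**Step 2: how often the conflict arises.** For k independent tests at 5%, P(at least one significant) = 1 − 0.95^k.

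| k | independent | pairwise correlation 0.3 | pairwise correlation 0.5 |
|---|---|---|---|
| 8 | 34% | 30% | 25% |
| 10 | 40% | 35% | 29% |
| 20 | 64% | 54% | 42% |

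The correlated columns were simulated with equicorrelated normal test statistics. Textbox 1 lists eight moderator entries recorded before randomisation. Some of them hold several variables, and baseline outcome scores come on top.

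**Step 3: what the rule does to error and power.** Simulation of 40,000 trials per setting, 114 complete cases per arm, one baseline covariate with correlation r to the outcome, and no imputation. Test-then-adjust means ANCOVA if the baseline t test has p < 0.05, and otherwise the plain t test.

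| r | size, test-then-adjust | power, t test | power, test-then-adjust | power, ANCOVA always |
|---|---|---|---|---|
| 0.3 | 4.4–4.7% | 85% | 86% | 88% |
| 0.5 | 4.1–4.4% | 85% | 86% | 93–94% |
| 0.7 | 3.4–3.7% | 85–86% | 87% | 99% |

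Ranges cover repeated simulation runs. A hand check of the last column uses Φ(d/√(1 − r²) × √(n/2) − 1.97), with √(114/2) = 7.55:

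- r = 0.3: Φ(0.419 × 7.55 − 1.97) = Φ(1.20) = 88%
- r = 0.5: Φ(0.462 × 7.55 − 1.97) = Φ(1.52) = 94%
- r = 0.7: Φ(0.560 × 7.55 − 1.97) = Φ(2.26) = 99%

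**Step 4: whether the choice of text matters.** In the roughly 5% of simulated trials where this one covariate differs significantly, the t test and the ANCOVA disagree on significance. Under no effect they disagree in about 9% (r = 0.3), 18–19% (r = 0.5) and 31–34% (r = 0.7). At d = 0.4 the figures are about 16%, 27–28% and 37–39%.

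**The case against.** The strongest case on the other side has five parts.

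- **A baseline-adjusted estimate is promised anyway.** This is true: the ANCOVA on baseline scores is prespecified for all outcomes, and baseline data also enter the imputation model. A reader should not infer that baseline PHQ-9 is ignored throughout. The point is confined to the primary model.
- **No error rate is broken.** This stands. A reader might infer that test-then-adjust inflates type I error, but the simulated size is below 5% in every setting. One can also show that an unadjusted t test rejects in about 7% of null trials when the baseline imbalance lies between |z| = 1 and 1.96 (r = 0.5). That is a property of any unadjusted t test, it is offset by about 3% when |z| ≤ 1, and it would remain if the rule were deleted and the t test kept. It is no argument against the rule.
- **The planned power is met.** This also stands. The rule gives 86–87% against a target of 85%, so the loss is a gain not taken. At r = 0.3 it is only about two points. If missingness stays near the 20% reported under Results and recruitment reaches 570, then 570 × 0.80 / 2 = 228 per arm would give about 99% power unadjusted.
- **64% is the top of an assumed range.** Agreed. It needs 20 independent tests. Stratification also limits imbalance in sex, diagnosis and previous treatment.
- **The plan can be carried out.** It can, if no baseline test is significant. The conflict is conditional, so the plan cannot be called unworkable outright.

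None of this reconciles adjustment in every analysis with a t test. A separate analysis plan may add detail, but the rule is stated here and contradicts what is stated beside it.

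**Conclusion.** The point holds in a limited form. The protocol lets chance imbalance decide the covariates of the primary analysis, and that instruction is incompatible with the t test it names as soon as one baseline difference is significant. Under independent 5% tests this happens in about 34% to 64% of trials for 8 to 20 variables, and less often with correlated or stratified variables.

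The consequences are a primary model that is not fixed in advance and precision given up. The power forgone is roughly 2, 7–8 and 11–12 percentage points at assumed correlations of 0.3, 0.5 and 0.7 with 114 per arm, and less if more participants are analysed. Type I error inflation is not among the consequences. The sample size is not in error.

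**What to change.** Before unblinding:

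1. In Statistical Analysis, delete the sentence on testing baseline differences. Report baseline characteristics by group descriptively, without p-values.
2. In Sample Size and Statistical Analysis, replace the t-test statements with one prespecified primary model: ANCOVA on the multiply imputed data, adjusted for the baseline score of the outcome and the stratification factors (sex, diagnosis, previous treatment), with sparse levels pooled by a stated rule.
3. Among the sensitivity analyses, exchange the roles: the unadjusted t test takes the place now held by the ANCOVA.
4. Keep N = 570 and describe it as a conservative calculation based on the unadjusted t test.

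All three places must change together. Removing the sentence and adding covariates while the t-test statements remain would recreate the contradiction. Deleting the rule and keeping the t test as primary would also remove the conflict, but without the gain in precision.

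The cost is a protocol amendment during recruitment (275 participants included at the reported date), which Ethical Considerations requires to be notified to the ethics committee and the trial registry. Neither data collection nor sample size changes.
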